## Abstract

**Background:**

Despite the high prevalence of subthreshold depression in patients with type 2 diabetes, evidence on cost-effectiveness of different therapy options for these patients is currently lacking.

**Methods/Design:**

Within-trial economic evaluation of the diabetes-specific cognitive behaviour therapy for subthreshold depression. Patients with diabetes and subthreshold depression are randomly assigned to either 2 weeks of diabetes-specific cognitive behaviour group therapy (n = 104) or to standard diabetes education programme only (n = 104). Patients are followed for 12 months. During this period data on total health sector costs, patient costs and societal productivity costs are collected in addition to clinical data. Health related quality of life (the SF-36 and the EQ-5D) is measured at baseline, immediately after the intervention, at 6 and at 12 months after the intervention. Quality adjusted life years (QALYs), and cumulative costs will be estimated for each arm of the trial. Cost-effectiveness of the diabetes-specific cognitive behaviour group therapy will be analysed from the perspective of the German statutory health insurance and from the societal perspective. To this end, incremental cost-effectiveness ratio (ICER) in terms of cost per QALY gained will be calculated.

**Discussion:**

Some methodological issues of the described economic evaluation are discussed.

**Trial registration:**

The trial has been registered at the Clinical Trials Register (NCT01009138).

## Background

Depression is a highly prevalent disorder with a substantial impact on quality of life and societal cost [1,2]. This applies in particular to patients with diabetes, since depression has been shown to be more prevalent among these patients as compared to those without diabetes [3-5]. Previous research demonstrates that comorbid depression in patients with diabetes is associated with poor self care, i.e. adherence to medication, diet, exercise and smoking cessation [6-8], additive functional impairment and work disability [9], poorer glycaemic control [10], higher risk of microvascular and macrovascular complications [11,12], decreased quality of life [13], and higher mortality [14,15] as compared to patients with diabetes only. Many studies also found higher overall health care cost in depressed patients, not explained by higher mental health treatment costs alone. This association persisted even after adjustment for comorbid medical conditions [see e.g. [7,16-19]]. A US study [17] found 4.5-times higher total annual healthcare costs for Medicare patients with diabetes and comorbid depression than for diabetic patients without depression ($247,000,000 and $55,000,000, respectively; *P *< 0.0001 (cost adjusted to reflect August 2001 dollars).

Hence, the more effective depression treatment might not only improve health outcomes, but also reduce total health service utilization and therefore costs. Put differently, additional costs for improved depression treatment could be offset by reduction in other healthcare costs. In the IMPACT trial [20] for example, systematic depression treatment in older adults with diabetes had significant clinical benefit with no increase in overall healthcare costs. The Pathways Study [21] also found that over a 2-year period the increased costs associated with enhanced mental health treatment were offset by savings in total medical expenditures.

Cost-effectiveness of treatment options for depression has been mainly evaluated for major depression co-occurring with diabetes. However, there is a need to examine the cost-effectiveness of therapies for subthreshold depression as well, since there is evidence that about 20% of patients with diabetes have elevated depressive symptoms without meeting criteria for major clinical depression [4,5]. In what follows, a within-trial economic evaluation of a diabetes-specific cognitive behaviour therapy in patients with type 2 diabetes and subthreshold depression is outlined.

## Methods/Design

### Clinical trial

The clinical trial is carried out as randomised clinical trial comparing a diabetes-specific cognitive behaviour group therapy (DS-CBT) to a standard diabetes education programme (DEP). The trial is carried out in the in the Diabetes Centre Mergentheim, Germany, where about 6500 diabetic patients are treated annually. Approval for the study was granted by the local Medical Ethics Committee (Ethikkommission der Ärztekammer des Landes Baden-Württemberg). Primary endpoint of the clinical trial is the reduction of subthreshold depression at the 12 months follow up. Secondary variables are improvement of glycaemic control (HbA1c), health related quality of life (SF-36 and EQ-5D), diabetes related distress, and diabetes self-management. Assessments take place before the intervention (baseline), after the core intervention (at 2 weeks), and at 6 and 12 months of the trial.

### Sample size calculation

A remission in 65% and 40% of cases is assumed under the DS-CBT and DEP respectively. To detect a statistically significant difference with a power (1-β) of 90% (2-sided t-test, α = 0.05) 83 patients in each treatment group are required. Assuming a loss to follow-up of 20%, 104 patients in each arm of the trial are needed.

### Study sample

Patients with type 2 diabetes and elevated depressive symptoms (ADS > 22) [22], but without clinical depression according to Composite International Diagnostic Interview [23], 18 to 70 years of age who gave informed consent are included into the trial. Exclusion criteria comprise treatment with anti-depressant drugs, diagnosis of acute psychiatric illness and severe somatic illness.

### Interventions

Trials participants are randomly assigned either to the intervention group that receives the DS-CBT in addition to the standard diabetes education programme or to a control group that receives only standard diabetes education programme offered by the Diabetes Centre Mergentheim. The DS-CBT consists of 10 lessons of 45 minutes each, delivered in 5 sessions of 90 minutes in a group setting within a period of 2 weeks. Each DS-CBT group consists of minimum 3 and maximum 8 members. The DS-CBT is based on an evaluated German manual of cognitive behaviour therapy [24], which has been modified according to diabetes-specific topics (coping with self monitoring, self injecting of insulin, reactions of others to diabetes, coping with late complications, hypoglycaemia problems, keeping a healthy diet, barriers to lifestyle modification). Furthermore, 4 telephone contacts within the following year are offered as booster sessions in addition to the 5 sessions of the "core intervention". The diabetes education programme includes continuous education and group sessions to optimise the diabetes management as well as workshops and lessons with diabetes-specific topics.

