### Statistical analysis of costs and effects

Mean total costs, health sector costs, patient costs and productivity costs as well as corresponding cost differences between the DS-CBT group and DEP group will be calculated. Sampling uncertainty (95% confidence intervals) will be estimated using bootstrap procedure because cost data are non-normally distributed.

Effect in terms of QALYs will be analysed using linear regression on type of intervention and - if necessary - on baseline utility score, which has been shown to be important for the unbiased assessment of mean QALY differences between treatment groups [32].

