### Determining cost-effectiveness

If a significant impact of DS CBT on both effects and costs is demonstrated, ICER will be estimated in terms of costs per QALY gained. ICER will be estimated for the total cost (health sector costs plus patient costs plus societal productivity costs) and for the health sector costs only (statutory health insurance perspective). The non-parametric bootstrap method will be employed to generate confidence intervals around the ICER estimates derived from the study sample [38,39]. Uncertainty surrounding the ICER will also be presented on the cost-effectiveness plane [40,41] and as the cost-effectiveness acceptability curve [42,43].

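### DS-CBT is given in therapy groups, but the sample size and QALY regression assume independent patients and no group level is stated for the bootstrap; if outcomes correlate within groups, intervals are too narrow and power falls below 90%

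*Protocol article*

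**What the plan says.** **Delivery (protocol article, Interventions).** The core DS-CBT is "delivered in 5 sessions of 90 minutes in a group setting within a period of 2 weeks". On group size: "Each DS-CBT group consists of minimum 3 and maximum 8 members". Both arms also receive the diabetes education programme (DEP), which itself contains some group sessions of unstated size.

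**Sample size (Sample size calculation).** "A remission in 65% and 40% of cases is assumed under the DS-CBT and DEP respectively", with "power (1-β) of 90% (2-sided t-test, α = 0.05"), so that "83 patients in each treatment group are required". The only inflation is for attrition: "Assuming a loss to follow-up of 20%, 104 patients in each arm of the trial are needed".

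**Analysis (Statistical analysis of costs and effects; Determining cost-effectiveness).** QALYs are regressed on treatment arm and, if needed, baseline utility. For costs: "Sampling uncertainty (95% confidence intervals) will be estimated using bootstrap procedure because cost data are non-normally distributed". For the cost-effectiveness ratio: "The non-parametric bootstrap method will be employed to generate confidence intervals around the ICER estimates derived from the study sample". Neither sentence names the unit to be resampled.

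The sections on imputation and sensitivity analyses do not mention therapy groups. No ICC, design effect or number of groups appears anywhere in the article.

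**The concern.** Patients treated in the same DS-CBT group share sessions, group dynamics and presumably the therapist, so their outcomes may be more alike than those of patients in different groups. On the cost side, intervention resource use such as staff time is taken from therapy protocols. If a session's staff time is divided among the attendees, that cost component is nearly identical within a group.

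With positive correlation, 83 patients in the DS-CBT arm carry less information than 83 independent patients. The consequences would be:

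- Standard errors for remission, QALYs and costs that ignore the grouping are too small, and tests reject too often.
- The bootstrap interval for the ratio and the acceptability curve look more certain than they should.
- The condition in Determining cost-effectiveness, that the ratio is estimated only if effects and costs both differ significantly, is met too easily.
- The 90% power for remission is not reached.

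**Working it through.** **1. Inputs.** From the article: remission 65% and 40%, two-sided α = 0.05, power 90%, 83 evaluable and 104 enrolled per arm, 20% loss, group size 3 to 8. Assumed here: ICC 0 to 0.10; mean group size m = 5.5 (midpoint of the permitted range) or 8 (the maximum); clustering in the DS-CBT arm only.

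**2. Number of groups.** 104/8 = 13 groups if all are full. 104/3 = 34.7, so at most 34 if all are near the minimum. For 83 evaluable patients, 83/8 ≈ 10 and 83/5.5 ≈ 15.

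**3. Reproducing the stated figure under independence.** Pooled formula:

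n = [1.96·√(2·0.525·0.475) + 1.2816·√(0.65·0.35 + 0.40·0.60)]² / 0.25² = (1.384 + 0.876)² / 0.0625 ≈ 81.8, so 82.

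The arcsine formula gives 82.06, so 83. Then 83/0.8 = 103.75, so 104. The stated figures are therefore reproduced with a design effect of 1, and the step from 83 to 104 is used up by loss to follow-up.

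**4. Power with therapy groups.** With DE = 1 + (m − 1)·ICC applied to the DS-CBT arm only:

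- SE under the null = √[0.525·0.475·(DE + 1)/83]
- SE under the alternative = √[(0.2275·DE + 0.24)/83]
- Power = Φ[(0.25 − 1.96·SE under the null) / SE under the alternative]

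At ICC 0: (0.25 − 1.96·0.0775)/0.0751 ≈ 1.307, power 90.4%. At ICC 0.05 and m = 5.5: DE = 1.225, (0.25 − 1.96·0.0818)/0.0791 ≈ 1.135, power 87.2%.

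**5. Type I error if grouping is ignored.** With equal arms and equal outcome variances: 2·Φ[−1.96·√(2/(1 + DE))]. At DE = 1.225 this is 2·Φ(−1.858) = 6.3%.

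| ICC | DE, m = 5.5 (8) | Power at 83 per arm | Unadjusted type I error |
|---|---|---|---|
| 0 | 1 (1) | 90.4% (90.4%) | 5.0% (5.0%) |
| 0.02 | 1.09 (1.14) | 89.2% (88.4%) | 5.5% (5.8%) |
| 0.05 | 1.225 (1.35) | 87.2% (85.3%) | 6.3% (7.1%) |
| 0.10 | 1.45 (1.70) | 83.8% (80.1%) | 7.7% (9.2%) |

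Power drops below 90% once the ICC exceeds about 0.007 (m = 5.5) or 0.004 (m = 8). The column for 8 is an upper bound: if all 13 groups are full and 83 patients remain, the mean analysed group is 83/13 = 6.4, and power at ICC 0.05 is 86.5% (DE = 1.27).

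**6. Does resampling groups cure it?** Simulation with a normal outcome clustered in one arm and 95% nominal coverage, at ICC 0.05 with 10 groups of 8. Ignoring groups covers about 92 to 93%. A percentile bootstrap of whole groups without correction also covers only about 92 to 93%. An interval from the variance between group means with small-sample (Satterthwaite) degrees of freedom covers about 95%. With 15 groups of 6 the pattern is the same (about 92 to 94% for the first two, about 94% for the third). At ICC 0.10 the uncorrected group bootstrap gains roughly 2 points but still falls short. Simulation error is about half a point.

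**The case against.** **The harm is conditional.** A reader might infer that the intervals are too narrow and that type I error exceeds 5% as plain facts. The article does not support that: both need a positive ICC, and none is given. Contact in the core therapy is five sessions in two weeks, while remission, QALYs and costs are assessed over 12 months, so the correlation may be small. At ICC 0.02 the power loss is under 2 points from 90%. This objection stands.

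**The bootstrap unit is inferred.** A reader might also infer that the bootstrap resamples individual patients. The article does not say so, and a fuller analysis plan could specify groups or robust standard errors. This stands for the bootstrap. It does not remove the point for the sample size, which is fixed at a design effect of 1, or for the QALY regression, whose stated terms include no therapy group.

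**The power refers to remission.** It does not describe QALYs, costs or the ratio, and the Discussion already says that cost differences need larger samples. This is correct; for the economic outcomes the concern is the standard errors.

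**Other power figures are possible.** With unpooled variances, power at ICC 0.05 is 88.5% (m = 5.5) or 86.8% (m = 8). That formula requires only 79 per arm, so it does not reproduce the stated 83; the pooled figures are the consistent ones.

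**DEP has group sessions too.** Treating DEP patients as independent is itself an assumption. With groups of 8 and ICC 0.05 in both arms, power would be 80.0%. Whether DEP groups mix the two arms is not stated, so no net effect can be claimed.

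**Good retention would restore power.** With all 104 per arm analysed, power at ICC 0.05 stays at 92.2% even for groups of 8. But the article reserves those patients for loss, and retention does not correct an understated standard error.

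**Conclusion.** The point holds in conditional form. The article fixes group delivery in one arm, while its sample size and stated QALY model assume independent patients, and it states no group level for the bootstrap. At an assumed ICC of 0.05, power is about 85 to 87% rather than 90%, and an unadjusted 5% test runs at about 6 to 7%. At ICC 0.02 the effect is minor; at 0.10 it is material (power 80 to 84%, type I error 8 to 9%).

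These figures assume clustering in the DS-CBT arm only, mean group sizes of 5.5 to 8, 83 evaluable patients per arm and the pooled normal approximation. The document supports neither a particular ICC nor a claim that the results will in fact be wrong. It is worth acting on because the correction is cheap and has to be arranged while group membership can still be recorded.

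**What to change.** 1. Record the therapy-group ID for every DS-CBT patient.
2. Analyse QALYs and costs with a partially nested model: a random therapy-group effect in the DS-CBT arm only, with small-sample degrees of freedom (for example Satterthwaite or Kenward-Roger). Group-robust standard errors with a small-sample correction are an alternative.
3. In the bootstrap, resample whole therapy groups in the DS-CBT arm and individual patients in the DEP arm, keep each patient's cost and QALY together, and correct for the small number of groups. Without that correction the interval under-covers with about 10 to 15 groups.
4. State that the 90% power assumes no within-group correlation, or restate it as about 85 to 87% (groups of 5.5 to 8) at an assumed ICC of 0.05. The sample size need not change.
5. If separate DEP group IDs exist, examine clustering there as a sensitivity analysis.

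The cost is one ID variable, which the centre should already know, and some analysis wording. Intervals become slightly wider and the stated power slightly lower.

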### Within-trial economic evaluation

The objective of the economic evaluation, which is conducted alongside the trial, is to estimate the cost-effectiveness of the DS-CBT in terms of costs per quality adjusted year (QALY) from the perspective of the German statutory health insurance and from the societal perspective. To this end an incremental cost-effectiveness ratio (ICER) will be calculated, i.e. the ratio of the difference in costs between DS-CBT and DEP groups divided by the difference in QALYs gained in each group. Under statutory health insurance perspective on cost, ICER will be calculated using health sector costs only. Adopting the societal perspective, also patient costs and societal productivity costs will be added to the calculation of the ICER.

### Estimating effects of intervention in terms of QALYs

For the purposes of economic analysis, measures comparable across various interventions as well as across different disease areas are preferred. Most popular outcome measure for this purpose are the quality adjusted life-years (QALYs), which explicitly combine length and quality of life in a single measure, weighting survival (a set of health states) by utility scores. Utility weights reflect preferences for a particular health state and are measured on a scale from 0 to 1, where 0 and 1 represent death and full health, respectively [25]. Although the trial does not include a utility measurement as part of its protocol, it does include the SF-36 and the EQ-5D questionnaires measuring health related quality of life. Standardized algorithms exist to translate EQ-5D and SF-36 scores into utility weights suitable for calculation of QALYs [26-28].

More than 15 value sets are available for scoring the EQ-5D, based on rating scale and time trade-off (TTO) valuation derived from general population surveys in various countries (including the United Kingdom, Germany, and the United States) [28]. In this study the scoring function derived from a survey of the general population in Germany will be used to calculate utility weights from EQ-5D responses [29].

Brazier and colleagues reported work on deriving a reduced health status index from the SF-36 that they termed the SF-6D [30] and more recently, they have published an algorithm that allows the estimation of utility weights for all states of the SF-6D index [31]. Following this published algorithm, SF-36 scores observed in the trial will be converted to utility weights. Since the values underlying this algorithm were obtained in the United Kingdom, utilities derived from SF-36 scores will be only used to perform a sensitivity analysis.

The SF-36 and EQ-5D will be administered at baseline, immediately after the intervention, at 6 months and at 12 months after the intervention (see Table 1). Hence, a maximum of four possible observations for SF-36 and EQ-5D scores and derived utility weights will be available for each patient enrolled in the trial. QALYs will be calculated assuming linear interpolation between measurement points and calculating the area under the curve to give a number of QALY gained per patient over the trial period [25].

**Table 1 T1:** Endpoints, measurement instruments and time of data collection

Endpoint	Questionnaire	Time of measurement			
		Baseline	2 weeks	6 months	12 months
QALYs	EQ-5D SF-36	**x**	**x**	**x**	**x**
Health sector costs	Health care utilisation and cost questionnaire	**x**		**x**	**x**
Patient costs	Health care utilisation and cost questionnaire	**x**		**x**	**x**
Productivity Costs	Health care utilisation and cost questionnaire	**x**		**x**	**x**

### Measurement of resource use

Resource use and costs directly associated with DS-CBT and DEP (e.g. staff time) will be derived from the therapy protocols. Information on the utilisation of other healthcare services will be obtained from trial participants by means of a cost questionnaire, which was developed for the study and incorporated into the case report files of the trial. The questionnaire is administered before the intervention (baseline), at 6, and 12 months of the trial and refers to the previous 6 months (see Table 1). The cost form includes structured no/yes questions on the utilisation of different medical services under the following categories: primary care visits, visits to emergency departments, visits to specialists, hospital stays, medication, and other therapies/paramedical care. If patients indicate that they received specific medical care over the past 6 months, they are asked to specify the volume: e.g. number of contacts with healthcare providers, number and length of hospitalizations, types and dosage of obtained medications. In the cost questionnaire patients are also asked to indicate whether health care services obtained by them were paid by the health insurance or self-paid, which makes an assessment of out-of-pocket expenses possible. Furthermore, the number of "days missed from work" will be registered with the cost questionnaire.

### Estimating costs

#### Health sector costs

To estimate costs from the statutory health insurance perspective, healthcare resource use due to interventions and other reported healthcare utilization (consultations, hospital days, etc.) will be multiplied by unit costs/prices. Currently, there are no German guidelines for costing in economic evaluations containing standard unit costs. Hence, healthcare resource use will be valued by unit costs/prices obtained from published sources and official statistics for Germany (e.g. charges and rates from administrative databases, pharmacy retail prices).

#### Patient costs

To estimate patient costs, reported consumption of healthcare services paid out of pocket will be multiplied by unit costs/prices available from official statistics and from providers.

#### Societal productivity costs

Days missed from work will be monetary valued according to the human capital approach [25].

### Statistical analysis of costs and effects

Mean total costs, health sector costs, patient costs and productivity costs as well as corresponding cost differences between the DS-CBT group and DEP group will be calculated. Sampling uncertainty (95% confidence intervals) will be estimated using bootstrap procedure because cost data are non-normally distributed.

Effect in terms of QALYs will be analysed using linear regression on type of intervention and - if necessary - on baseline utility score, which has been shown to be important for the unbiased assessment of mean QALY differences between treatment groups [32].

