### Imputation of missing information on costs and effects

Data will be analysed according to the intention to treat principle. A multiple imputation approach based on propensity scoring will be used to account for missing information with regard to effects and costs. Baseline variables (e.g. age, gender, cost at baseline, etc.) will be entered into a logistic regression to predict the chance of a missing value [33,34]. Available data will be arranged into quintiles based on this predicted probability (propensity score) and a replacement value for missing data will be selected at random from the available data points within the same quintile. By choosing a value at random within the same quintile the principle of multiple imputations could be employed, whereby each missing value is replaced by m > 1 simulated values [35-37]. Each of *m *resulting data sets will be analysed as described above and combined to produce a single result that takes uncertainty in the imputation process into account.

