## Discussion

In the context of the trial, it might be argued that, if true randomisation is achieved, any differences in cost between treatment arms can be attributed to the study intervention [45]. Hence, data on utilisation of a broad range of health services will be collected in the trial. This approach allows measuring any changes in resource use related to the interventions being compared. On the other hand, however, it may complicate the detection of statistically significant difference in health service costs, since the latter have been shown to be highly variable and therefore to require larger overall sample sizes [45,46].

Information on healthcare utilisation other than DS-CBT and DEP sessions will be collected by self-report by means of the cost questionnaire. To our knowledge no standard and validated instruments for collecting resource use data in clinical trials are available in Germany. Hence, we developed a data collection instrument specifically for this trial. The questionnaire was pilot tested, but has not yet been validated against other data sources. Recall bias may potentially occur, since resource use will be measured over the previous 6 months. However, there is no conclusive evidence regarding whether a prospective (a cost diary) or a retrospective (a questionnaire) instrument should be better applied and regarding an appropriate recall interval [45]. Van den Brink et al. found that for the assessment of healthcare utilization in economic evaluations alongside clinical trials, a cost questionnaire may replace a cost diary for recall periods up to 6 months [47] and that such patients' self-reports are a valid source of data on days of hospitalization and out-patient visits, whereas costs of medication may be underestimated [48].

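### Cost differences are planned without adjustment for the baseline 6-month cost that is already collected, which gives up precision in the ICER numerator

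*Protocol article*

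**What the plan says.** All references are to the Protocol article.

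- **Cost analysis** (Statistical analysis of costs and effects). Means are to be computed for total, health sector, patient and productivity costs, and "corresponding cost differences between the DS-CBT group and DEP group will be calculated". On uncertainty: "Sampling uncertainty (95% confidence intervals) will be estimated using bootstrap procedure because cost data are non-normally distributed". No model and no covariate is named.
- **QALY analysis** (next paragraph of the same section). "Effect in terms of QALYs will be analysed using linear regression on type of intervention and - if necessary - on baseline utility score".
- **Baseline cost data** (Measurement of resource use; Table 1). "The questionnaire is administered before the intervention (baseline), at 6, and 12 months of the trial and refers to the previous 6 months". Table 1 marks all three cost categories as measured at baseline.
- **Only stated use of baseline cost** (Imputation of missing information on costs and effects). "Baseline variables (e.g. age, gender, cost at baseline, etc.) will be entered into a logistic regression to predict the chance of a missing value". After imputation, the "resulting data sets will be analysed as described above and combined to produce a single result", so the cost analysis of the imputed data also has no covariate.
- **Use of the cost difference** (Determining cost-effectiveness). It is the numerator of the ICER, and the ICER is to be estimated only if the intervention significantly affects both effects and costs.
- **Cost variability** (Discussion). Of health service costs, the article says that "the latter have been shown to be highly variable and therefore to require larger overall sample sizes".

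**The concern.** Health care costs are usually skewed and tend to persist within a patient: heavy users before the trial are often heavy users during it. Prior cost on the same instrument is then a natural covariate. Without it, the between-patient variation that it could explain stays in the standard error, and a chance excess of heavy users in one arm goes straight into the estimated cost difference.

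Two features of this plan raise the stakes. The sample size rests on remission, not on costs, while the Discussion itself expects cost variability to make a significant difference harder to show. And because the ICER depends on a significant cost difference, precision on costs may decide whether the main economic result is produced at all.

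**Working it through.** **The plan's own figure.** The only sample size given is for remission: 65% versus 40%, two-sided 0.05, power 90%. With pooled variance under the null, n = [1.960·√(2·0.525·0.475) + 1.282·√(0.65·0.35 + 0.40·0.60)]² / 0.25² = 81.8, so 82 per arm against the stated 83. Allowing for 20% loss, 83/0.8 = 103.75, which gives the stated 104. The figure reproduces. No corresponding calculation is given for costs.

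**Inputs for the cost comparison.** n = 83 per arm with follow-up (Sample size calculation). The correlation r between a patient's baseline and trial-period cost is not in the documents. It is assumed here at 0.2, 0.3, 0.5 and 0.6.

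**Formulae**, in units of the SD of trial-period cost:

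- Unadjusted standard error: √(2/n) = √(2/83) = 0.155.
- Adjusted variance = unadjusted variance × (1 − r²), so the interval width is multiplied by √(1 − r²).
- Unadjusted sample size with the same precision: n/(1 − r²).
- Difference detectable with 80% power: (1.960 + 0.842) × 0.155 = 0.435 unadjusted, multiplied by √(1 − r²) when adjusted.
- Power, adjusted, for a difference that has 80% power unadjusted: Φ(2.802/√(1 − r²) − 1.960).
- Shift in the unadjusted difference from a one-standard-error imbalance in mean baseline cost: r × 0.155.

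| Assumed r | Variance removed | Interval narrower by | Equivalent n per arm | Detectable difference (SD) | Power | Shift (SD) |
|---|---|---|---|---|---|---|
| 0.2 | 4% | 2% | 86.5 | 0.426 | 81.6% | 0.031 |
| 0.3 | 9% | 5% | 91.2 | 0.415 | 83.6% | 0.047 |
| 0.5 | 25% | 13% | 110.7 | 0.377 | 89.9% | 0.078 |
| 0.6 | 36% | 20% | 129.7 | 0.348 | 93.8% | 0.093 |

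**Check under skewness.** Costs were simulated as lognormal (log SD 1, 83 per arm, no treatment effect, 6000 trials per setting) and analysed both ways. At cost correlations of about 0.20, 0.38 and 0.59, the ratio of adjusted to unadjusted standard error was 0.98, 0.91 and 0.78. The formula gives 0.98, 0.93 and 0.81. Linear adjustment therefore still helps when costs are skewed. Both estimators were centred on zero.

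**The case against.** *The article does not say that the difference is unadjusted, and an unseen analysis plan may add a covariate.* The first half is true: the reading is an inference from the wording. It is a strong one, because the same section describes a regression with a baseline covariate for QALYs and nothing of the kind for costs, and the imputation section then refers back to that description. The point is about the analysis as stated. It falls away if a fuller plan already adjusts.

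*An unadjusted mean difference with a bootstrap interval is valid in a randomised trial.* This stands. A reader might infer that the plan would let pre-existing cost differences pass as treatment effects. The documents do not support that: allocation is random, the estimator is unbiased, and its interval already allows for chance imbalance. What is lost is precision, and the chance to correct an imbalance seen in the actual sample.

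*Treating QALYs and costs differently is not an inconsistency.* This also stands. Baseline utility is the starting point of the QALY area under the curve and so enters that outcome directly, whereas baseline cost precedes the trial period and is no part of trial-period cost. The case for adjusting costs is efficiency, not symmetry.

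*The size of the gain is assumed.* It is. The documents give no correlation, which may also differ between health sector, patient and productivity costs.

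**Conclusion.** The point holds as a free improvement to a valid analysis, not as the correction of an error. Baseline cost is collected and the stated cost comparison does not use it. Over assumed correlations of 0.2 to 0.6, adjustment removes 4% to 36% of the variance of the cost difference. The benefit is slight below about 0.3 and material from about 0.5, where 83 per arm would do the work of about 111. The requirement of significance before the ICER is estimated makes this precision matter more than it otherwise would.

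Two further inferences should be avoided. The Discussion does not call cost variability the main limit of the evaluation: it also raises recall bias, an unvalidated questionnaire and possible underestimation of medication cost, and ranks none of them. Nor can the effect of an imbalance be put in euros from these documents. No cost SD is given, and a conversion would need the regression slope. A correlation cannot stand in for that slope here, since the baseline questionnaire covers 6 months and the trial-period cost 12.

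**What to change.** In Statistical analysis of costs and effects, state that each incremental cost (health sector, patient, productivity and total) is estimated by linear regression on arm and the matching cost for the 6 months before baseline. In every bootstrap replicate, resample patients with their costs and QALYs together and refit both this model and the QALY regression adjusted for baseline utility. Use the resulting pairs for the ICER and its interval, the cost-effectiveness plane and the acceptability curve. Apply the same analysis to each imputed data set. Keep the raw arm means as descriptive results.

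A plain gamma generalised linear model should not be offered as the alternative where zero costs occur. Zeros are plausible for out-of-pocket costs and for days missed from work, and the gamma distribution cannot take them.

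The cost is a change of wording, fixed before the cost data are analysed by arm. It needs no new data, visits or patients, because the baseline questionnaire is already in the case report forms.
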